### Measures

All primary and secondary outcome measures were assessed at baseline (Time 0), at the end of the intervention (Time 2), and at 3-month follow-up (Time 3). Data pertaining to theoretically-relevant variables [cf. 5,6] that may mediate changes were assessed at a mid-point data collection (week 6 of the program). The measures selected in the trial were:

#### Primary

*Eudaimonic well*-*being* was assessed at the contextual level by the Personally Expressive Activities Questionnaire [28] and at the life-domain level by items from previously validated questionnaires (i.e., the Personal Growth subscale [29], Prosocial subscale of the Strengths and Difficulties Questionnaire [30], Subjective Vitality Scale [31], and the Proactive Attitude Scale [32]. *Hedonic well*-*being* was assessed by the Positive and Negative Affect Scale for Children [33] and Life-Satisfaction in Adolescents Scale [34]. *Self*-*esteem* was assessed by Rosenberg’s scale [35], and *adaptive learning strategies* by the Patterns of Adaptive Learning Scale [36].

#### Secondary

Self-reported *physical activity levels* were assessed by the Physical Activity for Older Children and Adolescents Questionnaire (PAQ-A; [37]). *Smoking* and *Alcohol Intake* were assessed by subscales from the CDC’s Youth Risk Behavior Survey [38], while *dietary intake* was measured via the Food Frequency Questionnaire [39]. Additionally, *weight* and *height* (to provide Body Mass Index scores), and *objectively assessed physical activity level* data were obtained from a subsample of 103 participants. With physical activity in mind, data were collected using the ActiGraph GT1M unit. This unit has been validated in child and adolescent populations (e.g., [40]). The ActiGraph has no external controls or display, thus preventing user-feedback from influencing behavior.

#### Mediating variables

To explore the psychological processes underpinning the study hypotheses, the stems of the following inventories that have been successfully used in school-settings were slightly amended to target the BtBYCB program (intervention group) and PSHE (control condition): Perceptions of *Autonomy*-*Support*[41], *Basic Need Satisfaction* (viz., for autonomy, competence, and relatedness) [42], *Self*-*Regulation Towards Learning*[43], and the activity *Value*/*Usefulness*, *Choice*, *and Interest*/*Enjoyment* subscales from Intrinsic Motivation Inventory [44].

#### Moderating variables

Gender, age, biological maturation, SES, ethnicity, and access to facilities affect adolescent health behaviors and well-being. Thus, these variables were recorded and will be controlled for in the analyses.

### Supplementary research and methodologies

In addition to the primary research methodology (viz., the CRCT), two additional phases of work were conducted. These additional elements of research were:

#### Qualitative component

Pupils were randomly recruited from the intervention schools of the CRCT to partake in focus groups (i.e., 5 focus groups with 5 pupils in each). The main aims of this aspect of the work were to: (i) build an in-depth understanding of the “active ingredients” of the BtBYCB program that facilitate autonomy, competence, relatedness, and autonomous engagement with the intervention, (ii) investigate ways in which the participants’ need-satisfaction and motivation could be further enhanced, and (iii) explore ways in which the pupils think the program and its appeal could be improved. Across the intervention schools, five focus groups (involving 4 teachers in each school) and individual interviews (i.e., 5 × 1 headmaster per school) were also conducted so as to solicit views on the existing teacher education module, including (i) any difficulties experienced, (ii) whether any elements were not convincing, and (iii) ways in which the program could be better translated to practice (e.g., gaps in provision, content, etc.).

All participants were encouraged to talk openly about their experiences and the focus group content was transcribed verbatim and coded. As the focus group format can facilitate the recollection of experiences and thoughts (i.e., the input of one participant can stimulate the input of another) and for some the presence of others may inhibit a contribution to the process, a sample of the participants were randomly selected to respond to a brief summary of the emerging themes to result from the focus groups and asked to comment on, expand, and clarify the findings in *one*-*to*-*one* interviews cf. [45]. New data emerging from the individual interviews will also be subjected to further content analysis, and thematic extraction conducted cf. [46].

#### Mixed-methods component

The sample-frame for the mixed-methods component of the work consisted of participants that participated in the CRCT. Via a tertile split, participants were separated into three groups based on whether the program (i) was effective – i.e., a marked increase in reported scores were listed pre- to post; (ii) had no change – i.e., no noticeable change from pre- to post; and (iii) was counterproductive – i.e., a group for whom the program had an inverse effect pre- to post-. Participants meeting one of these criteria were short-listed, and participants selected from the list at random until the quota of interviewees was met. A total of 8 pupils per group were interviewed in each of the schools that received the BtBYCB intervention. The interviewer was blinded to the groupings to reduce bias. Semi-structured interviews were conducted to explore the process of change behind the responses of participants, and specifically, to extract potential triggers to change.

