**Methods/design:**

A two-arm cluster randomized controlled trial employing a wait-list control plus qualitative and mixed-method evaluations was used. Participants were school pupils from Years 7 and 8 (aged 11–13 years). Ten schools located in southwest England were randomly allocated to receive the BtBYCB intervention (n = 5 schools; 711 pupils) or a control condition (i.e., usual Personal, Social, and Health Education classes) (n = 5 schools; 622 pupils). Participants in the intervention condition received a program consisting of (i) a talk from an Olympian/Paralympian; (ii) 11 one-hour teacher-led PSHE classroom sessions in which pupils identified their aspirations, values, and interests and explored and acted on these via activities such as personal development planning, goal-setting, and peer-mentoring; and (iii) participated in a celebration event (e.g., second visit from Olympian/Paralympian and short individual presentations). Data were collected at baseline, post-intervention, and at 3-month follow-up.

Focus groups (pupils and teachers) and individual interviews (headteachers) were conducted in the 5 intervention schools to (i) gain an in-depth understanding of mechanisms of change; (ii) explore ways in which the participants’ motivation and engagement could be enhanced, and (iii) elicit user-feedback pertaining to how the program, content, and appeal could be improved.

A mixed-method approach was used to describe and explain the differing experiences of particular groupings within and across the intervention schools; i.e., those for whom the program was effective, those that experienced little, if any change, and those for whom the program led to an inverse effect.

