### Participants and setting

Secondary school children aged between 11 and 13 years attending 10 schools in the southwest of England served as participants in this project. Following ethical approval, parental consent, and participant assent, 1333 pupils were recruited for the CRCT using a cluster sampling approach. Pupils were randomly assigned by their school to either (i) BtBYCB intervention (n = 711 pupils from 28 classes) or (ii) a control group receiving standard PSHE lessons (i.e., standard care; n = 622 pupils from 30 classes). For the secondary analyses, a randomly selected sample of pupils and teachers were selected from each of the five intervention schools (n = 5). For the mixed-methods element, participants in each of the five schools were stratified by outcomes using a tertile split so as to acquire a purposeful sample encompassing different pupil experiences of the BtBYCB intervention (8 participants per grouping in each of the 5 intervention schools).

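### Tertiles of pre-to-post change are labelled as programme benefit, no change or inverse effect, which uncontrolled change in individual pupils cannot show

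*Protocol article*

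**What the plan says.** The Mixed-methods component section describes the grouping: "Via a tertile split, participants were separated into three groups based on whether the program (i) was effective". The first group is glossed as "a marked increase in reported scores were listed pre- to post", the second as "no noticeable change from pre- to post", and the third, called counterproductive, as "a group for whom the program had an inverse effect pre- to post". The section continues: "Participants meeting one of these criteria were short-listed, and participants selected from the list at random until the quota of interviewees was met". Eight pupils per group were interviewed in each intervention school, by an interviewer blinded to the groupings.

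Participants and setting describes the same step: "participants in each of the five schools were stratified by outcomes using a tertile split so as to acquire a purposeful sample". The Abstract (Methods/design) repeats the causal description, with "those for whom the program led to an inverse effect" as one of the groups to be described and explained. Secondary aim/objective does likewise.

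Two other sections matter. Control group says that control schools were measured at the same time points. Data Analyses adjusts for baseline and compares arms when it estimates the programme's effect.

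**The concern.** Two kinds of rule define the same groups. A tertile split is relative: it orders pupils and cuts the order into thirds. The descriptions attached to the thirds are absolute (scores rose, stayed or fell) and causal (the programme did it). The two agree only if the cut-points happen to fall where the descriptions need them.

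The causal part fails wherever the cut-points fall. A pupil's change from baseline to Time 2 mixes any programme effect with measurement error, with change that would have happened anyway, and with regression to the mean. The article describes no control reference and no baseline adjustment for this step, although the main analysis uses both.

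At stake is what the 8 × 3 × 5 = 120 interviews can be said to explain. They are meant to bring out triggers of change in pupils for whom the programme worked, did nothing or backfired. If the groups differ partly in where pupils started, themes that separate the groups may reflect high or low starting scores, yet be reported as reasons why the programme succeeded or failed.

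**Working it through.** **Inputs from the article.** 711 intervention pupils in 5 schools and a tertile split within school (Participants and setting); 8 interviews per group per school (Mixed-methods component); 0.25 SD as the difference the trial is sized for (Sample size calculation).

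**Assumptions.** The article gives no pre-post correlation r; I take 0.7, with a range of 0.5 to 0.9. Scores are normal with SD 1 at both times, and every pupil has the same true effect.

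**1. The plan's own figure.** It enters here only as a benchmark effect, with clustering taken at class level as the plan does. For 0.25 SD, two-sided 5% and 90% power, 337 pupils per arm are needed without clustering. The design effect is 1 + (25 − 1) × 0.05 = 2.2. Then 337 × 2.2 = 741.4 per arm, or 2 × 741.4 / 25 = 59.3 classes, against 58 stated. With 58 classes the detectable difference is 0.2525 SD, so the stated 0.25 is reproduced.

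**2. Size of the bottom third.** 711 / 3 = 237 pupils, or 711 / 15 = 47.4 per school on average. Neither r nor the true effect enters, so the existence and size of this group carry no information about harm.

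**3. What the thirds look like.**
- SD of change = √(2(1 − r)). At r = 0.7 this is √0.6 = 0.775.
- The cut-points of a normal variable into thirds lie at ±0.431 SD, and the mean of an outer third is ±1.091 SD.
- Mean change in the outer thirds with no effect = ±1.091 × SD of change. At r = 0.7 this is ±0.84.
- Correlation of baseline with change = −√((1 − r)/2). At r = 0.7 this is −0.387.
- Baseline shift of the outer thirds = 1.091 × 0.387 = 0.42 SD, below average in the top third and above average in the bottom third.
- Lower cut-point = effect − 0.431 × SD of change.

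| r | SD of change | Mean change of outer thirds, no effect | Baseline shift of outer thirds | Lower cut, no effect | Lower cut, gain 0.25 SD for all |
|---|---|---|---|---|---|
| 0.5 | 1.000 | ±1.09 | 0.55 | −0.43 | −0.18 |
| 0.6 | 0.894 | ±0.98 | 0.49 | −0.39 | −0.14 |
| 0.7 | 0.775 | ±0.84 | 0.42 | −0.33 | −0.08 |
| 0.8 | 0.632 | ±0.69 | 0.34 | −0.27 | −0.02 |
| 0.9 | 0.447 | ±0.49 | 0.24 | −0.19 | +0.06 |

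A simulation of 600,000 pupils per setting gave the same baseline shifts to within 0.01 SD.

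**4. Reading the table.** If every pupil truly gains 0.25 SD and r = 0.7, the bottom third still averages 0.25 − 0.84 = −0.59 SD and would be called counterproductive, although the programme helped each of them. For r from 0.5 to 0.8 the lower cut stays below zero, so the scores of these pupils did fall. At r = 0.9 it is above zero: P(change < 0) = 0.288, so (0.333 − 0.288) / 0.333, about 14%, of that group had rising scores.

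**The case against.** The strongest reply is that this is interview sampling. Participants and setting says the split served a purposeful sample, and taking the extremes and the middle is ordinary purposive practice. Effectiveness is judged between arms by ANCOVA and multilevel models, and no estimate uses these groups. All of that stands. The problem is limited to the labels and the inference drawn from them.

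Second, the short-listing sentence ("Participants meeting one of these criteria were short-listed, and participants selected from the list at random until the quota of interviewees was met") may mean that pupils also had to show an actual rise, no change or fall. That is possible, and the short list would then hold less than a third per group. The article states no threshold, and a condensed article may leave one to the full protocol. A threshold on change alone would still not supply a control reference or remove the baseline sorting.

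Third, with a 0.25 SD gain and r of 0.6 to 0.8, everyone in the bottom third did decline in score. This also stands: as a description of direction the label can fit, and only the attribution to the programme goes too far. A time trend common to all pupils likewise leaves the ranks unchanged and affects the labels only.

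A reader might infer that the trial will report a third of its pupils as harmed. The documents do not support this: no such proportion is reported or planned, and group sizes for interview are set by quota. A reader might also infer that the interviews would explain mostly noise. That depends on an assumed correlation and on how much true effects vary between pupils, neither of which is given, and some of the change will be real.

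**Conclusion.** The point holds for the supplementary mixed-methods component only. As written, a rank split of uncontrolled pre-to-post change is used to say for which pupils the programme was effective or had an inverse effect, and it cannot show either. That a rank split always yields a bottom third needs no assumption. The baseline sorting does: about 0.42 SD in opposite directions in the outer thirds at r = 0.7 with no effect, and 0.24 to 0.55 SD for r from 0.9 to 0.5, assuming normal scores with equal SDs. Interviewer blinding guards against leading questions but does not correct the grouping. The trial's effect estimates are untouched, and choosing contrasting groups for interview is sound. The matter should be corrected because it changes what the component can conclude and because the control data needed are already held.

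**What to change.** 1. In the control arm, regress the Time 2 score on baseline. For each intervention pupil, take the observed Time 2 score minus the score this model predicts. This removes the sorting by baseline and the change that control pupils also show.
2. Describe or re-classify the interviewees by that residual: highest, middle and lowest third within school. Where sampling is still open, keep the quota of 8 per group.
3. Call the thirds highest, middle and lowest change. Use better than, as, or worse than expected only where the residual is read against the control-arm prediction. A residual still contains measurement error, so it is not an individual programme effect.
4. Remove the effective and inverse-effect labels for individual pupils from the Abstract (Methods/design), Secondary aim/objective and Mixed-methods component, and from the reporting.

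Strict reliable-change cut-offs are not advised. With 711 / 5 = 142 pupils per school and no effect, 95% control-arm limits would place about 142 × 0.025 = 3.6 pupils beyond each limit, and 90% limits about 142 × 0.05 = 7.1, both short of the quota of 8.

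The cost is one small regression on data already held. Because the article reports the interviews as done, some interviewed pupils may move to another group and the groups may become unequal in size.

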### Data Analyses

Initially, analysis of variance (ANOVA) will be conducted to establish significant differences for the primary and secondary outcome variables between the two trial arms (allowing for the effects of nesting). Effect sizes, confidence intervals and confidence levels will be calculated. Changes from baseline in the primary and secondary end-points will be analyzed using an analysis of covariance (ANCOVA) model with the intervention as the main factor and baseline as a covariate. Further, multilevel modeling (using HLM 7 software; [47]) will be used to assess the strength of the effect of the intervention on the outcome variables (both primary and secondary) when controlling for nesting effects. Class and school will represent higher order units of analysis, and individual responses the lower order unit of analysis. In such analyses, it is possible to enter class and/or school as a random effect and all other variables as fixed effects.

For the focus groups and individual interviews, the recordings will be transcribed verbatim and analyzed using interpretive phenomenological analysis [48]. Statements will be coded by the investigators and a research assistant with themes within and across participants being extracted. Dependability and trustworthiness of the analysis will be demonstrated through; (i) researcher triangulation (i.e., discussion between researchers to establish all inferences are supported by the data), (ii) the triangulation of qualitative with quantitative data [49], and (iii) participant debriefing to check the researcher’s interpretations, and allow interviewees to make further comments.

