### Design

A single center CRCT employing a wait-list control group, supplemented by focus groups and a mixed methods process evaluation. The unit of randomization was school. Individual pupils will be the unit of analyses, yet we will take into account the nesting effects of schools and classes.

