### Sample size calculation

Using a sample size calculator software package [21], the 58 classes used in this work based on the average size of class (i.e., 25 pupils; [22]) permitted the detection, at the 5% significance and 90% power level, of a standard difference of 0.25 (i.e., .25 of a standard deviation can be detected with an intra-cluster correlation (ICC) of .05). In recognizing that some classes were smaller than the average 25 pupils, a more conservative estimate using the same criteria (5% significance with 90% power assuming an ICC of .05) showed that .27 of a standard deviation could be detected with 50 classes with 25 pupils in each cluster. The current sample size also accommodates analyses at school and classroom levels (i.e., pupils are nested within classes which are, in turn, nested within schools).

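### The baseline-adjusted ANCOVA is written without school or class nesting, contrary to the Design section; run that way, its type I error is about 18% rather than 5% at the protocol's own ICC

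*Protocol article*

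**What the plan says.** The Data Analyses section of the protocol article describes three between-arm analyses, each covering both the primary and the secondary outcomes.

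1. First, an "analysis of variance (ANOVA) will be conducted to establish significant differences for the primary and secondary outcome variables between the two trial arms", with a bracketed allowance for nesting.
2. Then, for change from baseline, an "analysis of covariance (ANCOVA) model with the intervention as the main factor and baseline as a covariate". No class or school term and no nesting allowance is given.
3. Last, multilevel modelling, which "will be used to assess the strength of the effect of the intervention on the outcome variables (both primary and secondary) when controlling for nesting". Its higher-order units are class and school.

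The section does not say which of the three decides whether the programme worked.

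The Design section states that the school was the unit of randomisation, and then: "Individual pupils will be the unit of analyses, yet we will take into account the nesting effects of schools and classes".

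**The concern.** Pupils in the same class or school tend to give similar outcomes. With 10 randomised schools, a pupil-level test that treats 1333 pupils as independent has too small a standard error and rejects a true null too often. On its wording, the ANCOVA is such a test. It is also the only one of the three whose description names baseline as a covariate, so it is a natural source for the headline effect estimate.

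The programme could then be reported as significantly improving a well-being outcome on the ANCOVA while a correctly clustered model shows no effect. Nothing in the section says which result would prevail.

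**Working it through.** **Inputs from the protocol article**
- Schools, classes and pupils (Abstract; Participants and setting): 5 schools, 28 classes and 711 pupils against 5 schools, 30 classes and 622 pupils. Mean class size is 1333/58 = 23.0; mean school size is 1333/10 = 133.3.
- ICC .05, applied to classes of 25 (Sample size calculation). No school ICC is given.
- Stated target: "at the 5% significance and 90% power level, of a standard difference of 0.25" SD with 58 classes, and 0.27 SD with 50 classes.

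**Step 1: reproduce the protocol's own figures** (two-sided test assumed)
- Design effect: DE = 1 + (25 − 1) × .05 = 2.2.
- 58 classes: effective n per arm = 58 × 25 / 2 / 2.2 = 329.5. Detectable difference = (1.960 + 1.282) × √(2/329.5) = 0.2525 SD. Power at 0.25 SD is 89.4%.
- 50 classes: effective n per arm = 50 × 25 / 2 / 2.2 = 284.1. Detectable difference = 0.272 SD. Power at 0.27 SD is 89.6%.

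Both figures reproduce. The sample size therefore rests on an analysis whose variance is inflated 2.2-fold for class clustering. The ANCOVA as written does not make that allowance.

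**Step 2: type I error of a pupil-level test that ignores clustering**

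Type I error ≈ 2 × [1 − Φ(1.96/√DE)], with DE = 1 + (m − 1) × ICC.

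| Level of clustering | m | ICC | DE | Type I error |
|---|---|---|---|---|
| Class (protocol ICC, actual size) | 23.0 | .05 | 2.099 | 17.6% |
| Class (protocol ICC, planned size) | 25 | .05 | 2.2 | 18.6% |
| School (assumed ICC) | 133.3 | .005 | 1.662 | 12.8% |
| School (assumed ICC) | 133.3 | .01 | 2.323 | 19.9% |
| School (assumed ICC) | 133.3 | .02 | 3.646 | 30.5% |
| School (assumed ICC) | 133.3 | .05 | 7.615 | 47.8% |

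Each row takes clustering at one level only.

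**Step 3: simulation of null trials**

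The formula ignores the effect of baseline adjustment on the residual ICC, so null trials with 10 schools and 58 classes were also simulated.
- All of the .05 at class level: the pupil-level ANCOVA rejected in 11% to 18% of trials (assumed pupil-level baseline correlation 0.5 to 0.7, cluster-level 0.5 to 0.9). A second simulation using 711 and 622 pupils gave about 18%.
- Class ICC .05 plus an assumed school ICC of .01: about 30%.
- All of the .05 at school level: 34% to 49%.

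**Step 4: how much comes from having several models**

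With every test clustered at school level, the chance that either the unadjusted or the baseline-adjusted test is significant was about 7% to 9%. One school-level test alone held 4% to 6%. The omitted clustering is therefore the main problem, and the number of models a minor one.

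**The case against.** The best defence is that the ANCOVA sentence is not a complete list of terms. The Moderating variables section says that gender, age, maturation, SES, ethnicity and access to facilities will be controlled for, and none of these appears in the ANCOVA sentence either. The absence of a school or class term is then not proof that it was excluded, and the general commitment in the Design section can be read as governing this model too. This stands as a reading of intent, and it is why the 18% is conditional. It does not remove the conflict: within one paragraph nesting is written into the analyses on either side and left out of this one, and an analyst following the text could properly fit the model without it.

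Second, naming the confirmatory model is commonly left to a statistical analysis plan, which is not shown. The order of the three analyses can also be read as a progression towards the multilevel model. This largely stands, so the lack of a decisive model is only a secondary point here.

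Third, a reader might infer that three competing models give each null outcome a 14% to 49% chance of a significant arm effect. The document does not support that as a plain consequence. It needs an unclustered ANCOVA, a rule that any one significant model suffices (stated nowhere), and an assumed split of the ICC between class and school. The range is not a bound either: with no clustering at all, the any-of-three rate was about 8% to 10%. At the top end the unclustered ANCOVA alone accounts for almost all of it.

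**Conclusion.** The point holds in conditional form. The ANCOVA is written without the nesting that the Design section promises and that randomisation by school requires. If it is run as written, type I error is about 18% at the protocol's class ICC of .05 and actual class size, roughly three and a half times the nominal 5% (17.6/5 = 3.5). Depending on how strongly baseline predicts outcome at pupil and cluster level, simulation puts it at 11% to 18%.

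Higher values rest on school-level clustering, for which the protocol gives no figure: about 20% at an assumed school ICC of .01, and about 48% only if an ICC of .05 applies at school level. If the ANCOVA is in fact clustered, the defect is one of wording, and what remains is the 7% to 9% from an undeclared choice between an unadjusted and an adjusted test. These rates are per outcome and time point and take no account of the number of outcomes.

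**What to change.** Replace the separate ANCOVA with one decisive multilevel model per outcome: follow-up score on arm and the outcome's own baseline value, with school and class nesting as the Design section promises, and inference suited to 10 randomised schools (for example, small-sample degrees of freedom). Take the effect estimate, confidence interval and p-value from this model alone. With baseline as a covariate, modelling the follow-up score gives the same arm effect as modelling change, so nothing is lost.

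Keep the ANOVA only as an unadjusted sensitivity analysis, with no claim of effectiveness attached.

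The cost is a few lines in the Data Analyses section and no new data. The downside is wider confidence intervals than an unclustered ANCOVA would show; the narrower ones would not be valid for this design.

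### Baseline adjustment and allowance for clustering are assigned to separate analyses, and no stated model commits to both

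*Protocol article*

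**What the plan says.** The Data Analyses section of the protocol article sets out three quantitative analyses.

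- **ANOVA.** It compares outcomes "between the two trial arms (allowing for the effects of nesting"). Baseline is not mentioned.
- **ANCOVA of change from baseline.** This is an "analysis of covariance (ANCOVA) model with the intervention as the main factor and baseline as a covariate". Nesting is not mentioned in that sentence.
- **Multilevel model.** It is introduced as a further step to assess the strength of "the effect of the intervention on the outcome variables (both primary and secondary) when controlling for nesting effects". No covariate list follows. The section adds only that "it is possible to enter class and/or school as a random effect and all other variables as fixed effects".

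Three other sections bear on the point.

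- **Measures** confirms that the covariate exists: "All primary and secondary outcome measures were assessed at baseline (Time 0").
- **Moderating variables** lists gender, age, biological maturation, SES, ethnicity and access to facilities, and says "these variables were recorded and will be controlled for in the analyses". The baseline score is not in that list.
- **Design** states "The unit of randomization was school" and gives a general undertaking: "Individual pupils will be the unit of analyses, yet we will take into account the nesting effects of schools and classes".

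**The concern.** Only ten schools were randomised, five to each arm. With so few units, the arms can differ at baseline by an amount that is not small beside the 0.25 SD the trial was sized to detect. The pupil's baseline score on the same measure is the obvious covariate to absorb such a difference, and it also removes outcome variance that is predictable before the intervention.

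A reader who follows the Data Analyses section literally would adjust for baseline in one model and for clustering in another. Naming the multilevel model as decisive would not settle this, because as described it controls for nesting and commits to nothing on baseline. At stake is the width of the confidence interval and how far the result of this one allocation depends on how the schools happened to fall.

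**Working it through.** **1. The three analyses side by side**

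| Analysis | Clustering named | Baseline named |
|---|---|---|
| ANOVA | yes | no |
| ANCOVA | no (general undertaking in Design only) | yes |
| Multilevel model | yes | no (permitted, not required) |

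No row has both.

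**2. The article's own figure**

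Inputs from Sample size calculation: 58 classes of 25 pupils, ICC 0.05, 5% significance, 90% power. A two-sided test is assumed, as sidedness is not stated.

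- Design effect = 1 + (25 − 1) × 0.05 = 2.2.
- Detectable difference = (1.960 + 1.282) × √(2 × 2.2 / n per arm).
- 58 classes, 725 pupils per arm: 0.253 SD (stated 0.25).
- 50 classes, 625 pupils per arm: 0.272 SD (stated 0.27).

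Both figures reproduce without any baseline adjustment. On the article's class-level basis, leaving baseline out does not undermine the stated power.

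**3. Precision forgone**

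If the baseline-outcome correlation is r at every level, including baseline multiplies the variance by (1 − r²), so the standard error falls by 1 − √(1 − r²). The article gives no r, so a range is assumed.

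| r | Fall in SE | Class-level detectable difference, 58 classes (0.253 without baseline) |
|---|---|---|
| 0.3 | 5% | 0.241 SD |
| 0.5 | 13% | 0.219 SD |
| 0.6 | 20% | 0.202 SD |
| 0.7 | 29% | 0.180 SD |

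**4. Chance baseline imbalance between 5 and 5 schools**

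Inputs: 10 schools, 58 classes (5.8 per school) and 1333 pupils (133.3 per school), treated as equal in size. The total ICC of 0.05 is kept and split between school (ρs) and class (ρc). The split is an assumption.

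Variance of the arm difference in SD units = (2/5) × [ρs + ρc/5.8 + (1 − ρs − ρc)/133.3].

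For ρs = 0.02 and ρc = 0.03: 0.4 × [0.0200 + 0.0052 + 0.0071] = 0.0129, so the SD of the baseline difference is 0.114. A gap above 0.125 SD (half of 0.25) in either direction is 0.125/0.114 = 1.10 standard deviations, with normal probability 27%.

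| ρs | ρc | SD of baseline difference | P(gap above 0.125 SD) |
|---|---|---|---|
| 0 | 0.05 | 0.079 | 12% |
| 0.01 | 0.04 | 0.098 | 20% |
| 0.02 | 0.03 | 0.114 | 27% |
| 0.03 | 0.02 | 0.127 | 33% |

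These probabilities ignore the stratified randomisation, which could lower them.

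**5. Illustration with school as the unit (t with 8 df)**

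At ρs = 0.02, the SE without baseline is 0.114 SD and power at 0.25 SD is 49%. With a common r of 0.5, 0.6 or 0.7, the SE is 0.098, 0.091 or 0.081 and power is 61%, 67% or 77%. With r = 0.6 for pupils and 0.7 for school and class, the variance is 0.4 × [(0.0200 + 0.0052) × 0.51 + 0.0071 × 0.64] = 0.0070, so the SE is 0.083 (27% smaller) and power is 75%. At ρs = 0.01, power goes from 61% to between 73% and 88% for r of 0.5 to 0.7.

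**The case against.** The strongest reply is that the text omits nothing by decision. The multilevel model is given a purpose and no covariate list. Its open wording on fixed effects can include the baseline score, and the preceding analysis has just named baseline as a covariate. The general undertaking in Design can be read as bringing clustering into the ANCOVA. A condensed article may also leave a full list of fixed effects to an analysis plan.

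Much of this stands. A reader might infer that the multilevel model is specified without baseline and that the valid estimate therefore loses precision. The documents do not support that: nothing excludes baseline from the multilevel model or clustering from the ANCOVA, so any loss depends on how the models are fitted. A reader might also infer that an unadjusted clustered estimate is biased. It is not: it is unbiased over randomisation, and its standard error reflects between-school variation if school is fitted as random. Nor is the sample-size figure wrong on its own basis. The 49% in the illustration comes mainly from an assumed school ICC and 8 degrees of freedom, a separate matter from baseline, and adding baseline does not restore 90% there. Finally, stratification by socioeconomic status, urban/rural location and size, together with the listed covariates, may reduce imbalance or its effect, although neither uses the outcome scores.

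What the reply does not remove is that the article does address baseline, and places it in the one analysis whose description leaves out nesting. Wording that says only what is possible commits to nothing.

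**Conclusion.** The point holds as one of commitment: baseline adjustment and clustering are stated in separate analyses, and no stated model is bound to have both. If the multilevel model is fitted as described, controlling for nesting only, the cost is forgone precision and less protection in the single allocation that occurred. It is neither bias nor a contradiction of the sample-size statement.

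The size is conditional. It is a fall in standard error of about 5% to 29% for an assumed common correlation of 0.3 to 0.7, and a 12% to 33% chance of a baseline gap above 0.125 SD for an assumed school ICC of 0 to 0.03 before stratification. At the low end the gain is slight; at the high end it matters for a trial of ten schools. A better model than any of the three stated is available from data already collected.

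**What to change.** In Data Analyses, state that the main multilevel model has arm, the pupil's baseline score on the same measure and the covariates listed under Moderating variables as fixed effects, with random intercepts for class and school. State that the reported effect size and confidence interval come from this model. Keep the ANOVA without baseline as descriptive.

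The cost is a sentence or two of text and no new data. The small downside is that pupils with no baseline score need simple imputation or are dropped, and the text should say which.
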